## Abstract

**Background:**

Cancer patients and survivors regularly feel anxious about cancer recurrence or death, even after the conclusion of medical treatment, and they are often highly physiologically and psychologically stressed. Massage therapy is one of the most widely used complementary and alternative therapies used in the hope of alleviating such stress and physical and psychological complaints and to improve health-related quality of life. This randomized phase III, two-armed, parallel group, clinical trial was designed after obtaining positive findings in a preliminary study. The primary objective is to verify the effects of continuous Japanese massage therapy, referred to as *Anma* therapy, for cancer survivors. The secondary objective is to confirm the immediate effects of a single *Anma* massage session for cancer survivors.

**Methods/Design:**

Sixty cancer survivors older than 20 years of age who have had histologically confirmed uterine cervical, endometrial, ovarian, fallopian tube or peritoneal cancer in the past, but with no recurrence for more than 3 years since receiving standard medical treatment, are being recruited by gynecologists in medical facilities. In the coordinating office, they are randomly allocated to two groups (*n* = 30 each): an *Anma* massage group receiving a 40-min *Anma* massage session once weekly over a 2-month intervention period (total of eight *Anma* massage sessions) and a control group being followed by medical doctors and receiving no *Anma* massage sessions. The primary end point is the severity of physical subjective symptoms that cancer survivors report in daily life, assessed using a Visual Analogue Scale. Secondary end points are urine and saliva analyses, psychological condition and health-related quality-of-life scores as determined on the basis of a self-report questionnaire.

**Discussion:**

Using the evidence-based findings of this trial, medical professionals should be able to explain the benefits conferred by *Anma* massage to cancer survivors and provide higher-quality information to better inform patients regarding their decisions about whether to receive such therapy.

**Trial registration:**

This trial is registered with the UMIN Clinical Trials Registry as UMIN000009097.

## Background

Since 1981, cancer has been the leading cause of death in the Japanese population. In 2011, there were 357,305 cancer deaths (28.5% of all deaths), 210,000 of which were men and 140,000 were women, and the number of such deaths is increasing because of the aging of the population [1]. In addition, the incidence of cancer is increasing, exceeding 700,000 (410,000 men and 290,000 women) according to the latest data [2]. It is estimated that the yearly average number of cancer deaths and cancer incidence for the period 2025 to 2029 in Japan will be approximately 230,000 men and 160,000 women and 530,000 men and 390,000 women, respectively [3]. Both the number of cancer deaths [4] and cancer incidence [3] for men are expected to slow after 2015, whereas for women these figures, especially regarding the incidence of cancers of the oral cavity and pharynx, kidney and urinary tract, uterus, lung, pancreas and cervix are expected to continue increasing at the present rate [4]. It is also known that early detection and progressive treatment options have improved the prognosis of cancer patients and increased the number of cancer survivors in Japan [5], and accordingly interest has been shifting from radical treatment options toward ensuring a better quality of life (QoL) for patients to cope with the disease [6].

Cancer patients and survivors regularly feel anxious about cancer recurrence or death, even after the conclusion of medical treatment, and it is known that they are highly stressed, both physiologically and psychologically [7-9]. Although 65% of men living with cancer are older than 65 years of age, 68.2%, 72.8%, 68.7% and 70.6% of women with breast, uterine, thyroid and ovarian cancer, respectively, are younger than 65 years old [5]. Because the time women live with cancer is thought to be longer than that of men, it may be especially necessary to provide enhanced physical and mental care to female cancer survivors.

Numerous studies on massage for patients with cancer have been conducted in Western countries in recent years. The findings of many of these studies imply that massage therapy may help to improve the physical and psychological symptoms of cancer patients [10-13], and patients receiving massage therapy in a pilot study reported improvements in stress and QoL [14]. Massage is, in fact, one of the most commonly used complementary and alternative therapies for cancer [15].

Japanese massage therapy, known as *Anma* therapy (hereinafter *Anma* massage therapy), is one of the most popular complementary and alternative therapies in Japan. It has long been used with the aim of improving or alleviating physical and psychological symptoms. With high expectations for *Anma* massage therapy, we previously conducted a preliminary study to assess whether *Anma* massage therapy confers physical and psychological benefits in five cancer survivors who had undergone surgery for uterine cervical or endometrial cancer (stages Ia1 to IIa) [16]. All participants received *Anma* massage therapy consisting of eight 40-min *Anma* massage sessions over 4 wk. In regard to immediate changes in variables after a single *Anma* massage session, physical subjective symptoms assessed using a Visual Analogue Scale (VAS) were significantly improved, state anxiety score and salivary cortisol were lowered and secretory immunoglobulin A (s-IgA) was significantly increased. In addition, after seven continuous *Anma* massage sessions, VAS score, anxiety score and depression score were all lowered. On the basis of these preliminary findings, we designed the present randomized trial to verify the effects of *Anma* massage therapy compared with no *Anma* massage therapy. The primary objective of the trial is to verify the effects of continuous *Anma* massage therapy for cancer survivors. The secondary objective of the trial is to confirm the immediate physical and emotional effects of a single *Anma* massage session.

## Methods and design

### Study design and setting

This study is a randomized, two-armed, parallel group clinical trial. The coordinating office is at Tsukuba University of Technology, Japan. Gynecologists in other medical facilities introduce the coordinating office to patients who meet the eligibility criteria and confirm they do not meet any exclusion criteria.

When patients show interest in trial participation, the gynecologists send an introduction form to the coordinating office by facsimile. The coordinating office calls the introduced patient to decide the date on which to meet to explain the trial, and the patient visits the office to be given information verbally on the trial and reads the written trial description. After the meeting, the patient submits the consent form by hand, facsimile or mail upon deciding to register for the trial. Accrual started on 12 October 2012, and the term for patient registration for the trial is within 2 years from this date. Sixty participants are planned to be recruited.

### Ethical consideration and study registration

The study protocol was designed in accordance with the World Medical Association’s Helsinki Declaration [17] and the Ethics Guidelines for Clinical Research of the Ministry of Health, Labor, and Welfare of Japan [18]. This trial was approved by the Medical Ethics Committee of Tsukuba University of Technology, Japan, on 27 September 2012 (Approval No. 5) and was registered with the UMIN Clinical Trials Registry as application UMIN000009097 on 12 October 2012.

### Eligibility criteria

The inclusion criteria are (1) histologically confirmed uterine cervical, endometrial, ovarian, fallopian tube or peritoneal cancer in the past; (2) no recurrence of such cancer for more than 3 years since receiving standard medical treatment; (3) older than 20 years of age at the date of registration for the trial; (4) patient’s doctor deems the patient to be eligible for the trial; and (5) receipt of written informed consent from the patient to participate in the trial. The exclusion criteria are (1) active infections; (2) serious concurrent disease of the heart, liver or kidney, etc.; and (3) severe mental disorders.

### Randomization

After finishing registration, the patients are allocated by block randomization by the coordinating office to continuous *Anma* massage therapy or no *Anma* massage therapy, except for a single *Anma* massage therapy intervention at the end of the trial period (Figure 1). Allocation adjustment factors are not set in the trial because of insufficient evidence at present regarding which factors affect the effectiveness of *Anma* massage therapy.

**Figure 1 F1:**
[figure not shown]
Trial Flow Diagram.

### Protocol treatment

#### Interventions

##### *Anma* massage therapy group

This group receives treatment by continuous *Anma* massage therapy according to the trial protocol. The protocol treatment is completed when the patient finishes receiving the final 40-min *Anma* massage session of a total of eight sessions given once weekly over a 2-month intervention period. *Anma* massage therapy techniques consist of standard versions of Japanese massage, mainly kneading with lesser amounts of stroking and pressing. *Anma* massage is performed through clothing, with the intensity of stimulation applied being within each person’s range of comfort. On a massage table, a full-body *Anma* massage excluding the face, head and abdomen is performed following the procedure described in detail in our previous studies [16,19,20], with a focus on the specific locations where patients want to improve physical symptoms. A therapist provides all massage sessions to avoid differences in technical capabilities. This therapist has a national massage practitioner license and over 20 years of experience and was the therapist involved in providing *Anma* massage treatment sessions in our previous studies [16,19,20].

##### No *Anma* massage therapy group

This control group is followed by their medical doctors as usual and do not receive the continuous *Anma* massage sessions. Patients visit the coordinating office and have a 40-min relaxing chat with a massage therapist while lying on a massage table, but without receiving a massage. Two months later they return to the office to receive a single 40-min *Anma* massage session.

### End points

The primary end point is the severity of subjective physical complaints that cancer survivors report in daily life as measured using a VAS. To assess the severity of subjective physical complaints, a sheet of paper (width 100 mm × height 40 mm) is given to the participant, and it is explained that the left edge of the paper represents no complaint and the right edge the most serious complaint that the participant can imagine. The participant records the seriousness of the degree of the subjective complaint at that time as a check mark on the paper. The length from the left edge to the check mark is measured and considered the VAS score.

The secondary end points of the study are as follows. (1) The score on the Profile of Mood State–Brief Japanese Version (POMS) questionnaire is used to assess immediate psychological effects. (2) The score on the Hospital Anxiety Depression Scale–Japanese version (HADS), a 14-item scale developed to assess anxiety and depression for particular cancer patients. (3) The score on the European Organization for Research and Treatment of Cancer QLQ-C30–Japanese version (EORTC QLQ-C30) scale, which was developed to assess health-related QoL, particularly in cancer patients. The subscales are global health status, functional scales (physical functioning, role functioning, emotional functioning, cognitive functioning and social functioning) and symptom scales (fatigue, nausea and vomiting, pain, dyspnea, insomnia, appetite loss, constipation, diarrhea and financial difficulties). (4) The score on the Measure of Adjustment to Cancer–Japanese version (MAC) questionnaire, because some studies [21,22] have reported a correlation between adjustment of cancer, QoL and mental health. Because some communication between the patient and massage therapist is commonly built into massage sessions, psychological adjustment to cancer (coping style to cancer) may change through such communication during continuous *Anma* massage therapy. (5) The level of 8-hydroxydeoxyguanosine and catecholamine (noradrenaline, adrenaline and dopamine) in urine is measured. (6) Levels of cortisol, chromogranin A and s-IgA in saliva are measured.

### Data collection

Data collection is performed on three occasions in the *Anma* massage group: before and after the first *Anma* massage session (measurements A and B) and before the last (eighth) *Anma* massage session (measurement C) (Figure 1). Data collection is conducted on four occasions in the control group: before and after the relaxing chat session (measurements D and E) and before and after the single *Anma* massage session (measurements F and G) at 2 months (Figure 1).

To assess the effects of continuous *Anma* massage sessions, changes in all end points between measurements A and C are compared with those between measurements D and F.

In addition, to confirm immediate changes following a single *Anma* massage session, which is the secondary objective of the trial, changes in VAS score, POMS score, and levels of 8-hydroxydeoxyguanosine, catecholamine (noradrenaline, adrenaline and dopamine), salivary cortisol, chromogranin A, and s-IgA between measurements A and B are compared with those between measurements D and E. Such changes between measurement F and measurement G are also considered as additional evidence to confirm the immediate effects of a single *Anma* massage session.

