### Statistical analysis

Analysis of pretreatment characteristics and efficacy analysis will be performed according to the modified intention-to-treat principle and will include all participants who receive at least one *Anma* massage session in the *Anma* massage therapy group and one relaxing chat in the no–*Anma* massage group. If necessary, we might also perform sensitivity analyses, adding all eligible patients who are introduced by medical doctors to the coordinating office but are not registered.

The primary end point is VAS score improvement over the 2-month study period. For primary analysis, we will use the analysis of covariance to compare the mean changes in VAS score over the 2 months between the *Anma* massage group and the no–*Anma* massage group, adjusting for the baseline VAS score and age. If we find other significant prognostic factors, we will use them as additional adjusting factors. We will also use a two-sample *t*-test with Satterthwaite’s approximation to compare the mean changes. We will also test the mean changes in VAS score for each group using a paired *t*-test. For these mean VAS score changes and their differences, we will also calculate two-sided 95% confidence intervals (CIs) to evaluate the clinical effects.

For the secondary end points, we will not consider multiplicity issues. In all analyses, categorical variables will be described in terms of frequency and percentage. The distributions of continuous variables will be described using means, SDs, medians, and minimum and maximum values. A two-sample *t*-test or paired *t*-test will be used to detect differences in continuous variables. Pearson’s χ^2^ test with continuity correction will be used to test differences in categorical variables. If these data are found not to be normally distributed, we will use in their place the Wilcoxon signed-rank test or the Mann-Whitney *U* test, respectively. All reported *P* values will be two-sided. All significance levels will be set at 0.05, and reported CIs will be 95%. In principle, we will use the available-case analysis for missing outcomes. SAS statistical software (version 9.3 or later; SAS Institute, Cary, NC, USA) will be used for all analyses.

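### The primary outcome is tied to the eighth visit in the Anma arm but to the calendar in the control arm, so early stoppers in the Anma arm have no scheduled outcome

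*Protocol article*

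**What the plan says.** The Data collection section lists three measurement occasions for the Anma arm: before the first session (A), after it (B), "and before the last (eighth) *Anma* massage session (measurement C"). For the control arm the follow-up measurements are dated by time: "measurements F and G) at 2 months". The section on the no-Anma group confirms this: "Two months later they return to the office to receive a single 40-min *Anma* massage session".

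For the effect of continuous massage, "changes in all end points between measurements A and C are compared with those between measurements D and F". The Statistical analysis section gives both arms the same horizon: "The primary end point is VAS score improvement over the 2-month study period".

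Two further statements bear on the point. The Anma therapy group section sets the final session as the last "of a total of eight sessions given once weekly over a 2-month intervention period". The Statistical analysis section admits to the modified intention-to-treat set anyone in the Anma arm with at least one session, and then says: "In principle, we will use the available-case analysis for missing outcomes".

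**The concern.** The two sides of the primary comparison have different anchors. C is defined by a treatment event and moves with attendance. F is defined by elapsed time and does not.

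Two things follow. First, the change may be measured over different lengths of time, and the protocol does not say how far C may drift when sessions are missed or postponed. Second, and more important, someone who stops after, say, session three is in the analysis set, but the stated schedule contains no later measurement for her. The available-case rule then removes her from the primary analysis of covariance. A control participant has one return visit to make; an Anma participant has to continue to the eighth visit.

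If people who stop are those who feel no benefit, the Anma mean is taken over a favourably selected group. The Discussion presents the trial as confirmatory and cites intention-to-treat analysis as protection against bias. That protection is weaker than it appears for the end point that matters most.

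**Working it through.** **Timing.** Sessions 1 to 8 at weekly intervals span 7 intervals, so C falls 7 × 7 = 49 days after A. Two months is 56 days if read as eight weeks, and up to 62 days as two calendar months. F is then 56 − 49 = 7 to 62 − 49 = 13 days later than C. If the eight sessions are instead spread over about two months, the gap largely closes. Postponed sessions move C later; nothing moves F.

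**Who contributes an outcome.**

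| | Anma arm | Control arm |
|---|---|---|
| Enters the analysis set | at least one session | the chat visit |
| Primary change | A to C | D to F |
| Condition for the second measurement | reaching the eighth visit | one return at two months |
| If that condition is not met | no scheduled C; dropped as unavailable | no F; dropped as unavailable |

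**Illustrative size.** The protocol has no figure of its own to reproduce here, and it gives no dropout rate. The inputs from the Sample size determination section are the SD of change, 19.6 mm, and 30 per group. Everything else is assumed: no true effect, no selective loss among controls, a loss *m* in the Anma arm, and a probability of stopping of 1/(1 + exp(−(a + k·z))). Here z is the change in SD units (positive = worse), k is the log-odds per SD, and a is set so that the overall loss is *m*.

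- Bias among those measured = −*m* × (mean change of stoppers)/(1 − *m*). For k = 1 and *m* = 10%, stoppers average 16.0 mm worse than the whole arm, so the bias is −0.10 × 16.0/0.90 = −1.8 mm. For *m* = 20% they average 13.6 mm worse: −0.20 × 13.6/0.80 = −3.4 mm.
- SE = 19.6 × √(1/(30(1 − *m*)) + 1/30), which is 5.20 mm at 10% and 5.37 mm at 20%.
- Two-sided type I error = Φ(−1.96 + |bias|/SE) + Φ(−1.96 − |bias|/SE).

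| Anma loss | Bias, k = 1 | Type I error | Bias, k = 0.5 | Type I error |
|---|---|---|---|---|
| 3% | −0.6 mm | 5.1% | −0.3 mm | 5.0% |
| 5% | −0.9 mm | 5.4% | −0.5 mm | 5.1% |
| 10% | −1.8 mm | 6.4% | −1.0 mm | 5.4% |
| 15% | −2.6 mm | 7.8% | −1.4 mm | 5.8% |
| 20% | −3.4 mm | 9.7% | −1.9 mm | 6.4% |

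Negative values favour massage. The calculation compares unadjusted mean changes; the planned adjustment for baseline VAS and age would remove the part of the selection that those covariates explain.

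**The case against.** The strongest reply is that a journal article condenses the protocol, and visit windows and follow-up after stopping are details it may leave out. That stands for the windows themselves: their absence is not the finding. But the two anchors are stated, and so are the list of three Anma measurements and the available-case rule. Together they leave early stoppers without a scheduled primary outcome.

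Other parts of the reply also stand:

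- **Completers only.** A reader might infer that outcomes exist only for those who complete treatment. The text does not say that. C precedes session eight, so the last session need not be received, and someone who attends late still has a C. The condition is reaching the eighth visit.
- **A fixed 12-day gap.** Day 49 against about day 61 is one reading. The protocol also speaks of a two-month intervention period, and the gap alone need not bias anything: the sample size section's base case assumes no mean change in controls over two months.
- **Loss in one arm only.** Controls must return for F and can be lost as well. Equal selective loss in both arms would cancel under no effect.
- **Direction.** People may also stop because they feel better, which would work against massage.
- **Intention-to-treat undone.** The analysis section openly claims a modified version with available cases. The scheme weakens that claim for early stoppers; it does not void it.

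**Conclusion.** The inconsistency is in the text: an event-anchored outcome in one arm, a calendar-anchored one in the other, and a single two-month end point declared for both. That early Anma stoppers fall out of the primary analysis follows from the stated schedule and the available-case rule.

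The harm is conditional. It needs some Anma participants to stop before the eighth visit, stopping to be related to poor change, and controls not to be lost in the same way. Under the assumed models it ranges from negligible (under 1 mm, type I error 5.0% to 5.4%, at 3–5% loss) to −3.4 mm and nearly 10% at 20% loss with the stronger selection. A reader might conclude that the primary result is already compromised. The documents do not support that, because they give neither a dropout rate nor a reason for stopping. The point is a cheap and worthwhile improvement, not a must-fix.

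**What to change.** Reconcile the sections on the Anma therapy group, the no-Anma group, Data collection and Statistical analysis so that C and F share one stated nominal time, counted from A and D, with a common window. Keep the present rule that both are taken before any session on the day.

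Collect at least the VAS and the questionnaires from every Anma participant at that time, however many sessions were attended, and keep these participants in the primary analysis of covariance. The treatment schedule itself is for the sponsor; only the outcome assessment needs re-anchoring. The article reports the trial as still recruiting, and an outcome that was never collected cannot be recovered in the analysis.

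The cost is a short amendment and a few mailed forms. There are two downsides. Some Anma participants will be measured after fewer sessions, or some days after their last one, which slightly dilutes the estimate and shifts it away from a purely on-treatment effect. A mailed VAS also differs in administration from one explained in person, so such values should be flagged and examined in a sensitivity analysis.
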